#### Intervention groups

Participants randomly assigned to the PREPARED program receive the informational intervention, which consists of an educational video and written handbook intended to be used together to inform patients’ decisions about their kidney disease treatment choices. These materials are provided to participants on a day when they do not receive dialysis in the dialysis center. Participants meet with trained research study staff during which time they are oriented to the book and watch the video. Study staff members also encourage participants to share the materials with their families and health care providers. Participants randomly assigned to the PREPARED plus Financial Assistance program receive the informational intervention at the time of enrollment in a similar fashion with a similar approach to the PREPARED assignment. In addition, participants in this group are invited to participate in the live kidney donor financial assistance program as described above.

### Data collection, follow-Up and outcomes

#### Measures assessed through interventions

All patient participants enrolled in the study are assessed using an in-person questionnaire at the time of recruitment and a structured telephone interview at baseline, 1 month, 3 months, and 6 months. Trained study staff administer all telephone interviews. For the informational and financial intervention arms, participants are contacted via telephone to determine whether they have viewed the materials provided to them (an educational video and written handbook for the informational intervention and the brochure for the financial intervention arm) again at home. Participants are also asked if they have shared or discussed the content of intervention materials with family members.

The primary outcome of interest is patients’ pursuit of LRT over six months of follow up. This outcome is measured as participants’ achievement of at least one of six key steps toward pursuing LRT, including: 1) execution of patient-family discussions about LRT; 2) execution of patient-physician discussions about LRT; 3) initiation of the recipient evaluation for LRT; 4) completion of the recipient evaluation for LRT, 5) identification of a potential live kidney donor, and 6) being listed at a transplant center. Pursuit of LRT will be assessed via questionnaires administered via telephone questionnaire at baseline, 1 month, 3 months and 6 months follow-up time periods. For participants reporting being registered on a transplant waiting list, we will contact transplant centers to determine whether there have been any live donor inquiries on behalf of the participant. We will also assess whether patient participants receive LRT and whether patient participants’ family members inquire about or use the financial assistance program (for those randomized to the PREPARED plus Financial Assistance arm).

Other measures include assessment of participants’ (1) knowledge of LRT; (2) interest in LRT; (3) perceived barriers to LRT; (4) preferred role in decision-making about LRT; (5) concerns about the risks of LRT to themselves and to donors [43-45]; (6) family structure and relationships [46]; (7) interest in other forms of renal replacement therapy (i.e., peritoneal dialysis or home-hemodialysis); (8) satisfaction with hemodialysis therapy; (9) depression and social support [47,48]; (10) financial stress [49]; (11) health literacy [50] and numeracy [51,52]; (12) trust in the medical system [53,54], (13) comorbid conditions [55] and (14) sociodemographic characteristics. For patient participants assigned to the PREPARED and PREPARED plus Financial Assistance groups, we also assess their perceptions of the helpfulness of the video and handbook. In all study groups, we also assess the number of donor inquiries on behalf of study participants at local transplant centers (Table 1).

**Table 1 T1:** Data collected at study baseline and follow up

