#### Target population and eligibility criteria

Our population includes English-speaking African American patients with ESRD who are age 18 years or older and who have initiated dialysis within one year prior to study enrollment. We exclude participants if they have dementia (assessed in-person) [42] or if they have a self reported history of prior kidney transplant, cancer within 2 years prior to recruitment, stage IV congestive heart failure, end stage liver disease, pulmonary hypertension, severe peripheral vascular disease, or chronic (debilitating) infections. We assess participants’ eligibility via questions administered by a research assistant in-person in dialysis units. After potentially eligible patients agree to participate, we request a release of medical records from each participant to confirm their eligibility for the study and to ascertain whether potential donors have contacted local transplant centers to be evaluated as donors on behalf of participants.

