#### Randomization

Using blind and secure allocation by computer, we randomly assign participants to one of three intervention arms: 1) control group (“Usual Care”, N=70); 2) the informational intervention (“PREPARED”, N=70); and 3) the informational plus the financial assistance interventions (“PREPARED plus Financial Assistance”, N=70). Randomization is blocked by recruitment site to ensure equal allocation within each dialysis facility.

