#### Sample size and power

We are aware of no other randomized controlled trials evaluating the effectiveness of informational (focused on shared decision-making) or financial interventions on commitment to LRT in incident dialysis patients. In our own work, an educational intervention resulted in patients’ greater pursuit of LRT (30% achieving new LRT behavior in Usual Care arm compared to 50% in education arm over 6 months) [19]. Our own previous work also demonstrated African Americans in the US general public were supportive of live kidney donors receiving reimbursement for expenses related to donation [24]. We anticipate the financial intervention, which addresses a common and tangible barrier to live kidney donation, may improve pursuit of LRT by an additional 10%. Based on these assumptions, we will have over 80% power to detect a trend of increasing pursuit of LRT across groups (e.g., 30% in Usual Care, 50% in PREPARED group, 60% in PREPARED plus Financial Assistance group) at 6 months. We will also have over 80% power to detect a 30% difference between the PREPARED group and the Usual Care group or the PREPARED plus Financial Assistance group and the Usual Care group individually with correction for multiple comparisons.

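### The one described procedure for finding live-donor inquiries applies to participants who report being wait-listed, a status the intervention may change, although a records release is requested from everyone

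*Protocol article*

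**What the plan says.** Three statements in the protocol article bear on how live-donor inquiries are found.

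- *Measures assessed through interventions* gives the procedure: "For participants reporting being registered on a transplant waiting list, we will contact transplant centers" to learn whether any live donor has inquired on the participant's behalf.
- Later in the same section, among the other measures: "In all study groups, we also assess the number of donor inquiries on behalf of study participants at local transplant centers".
- *Target population and eligibility criteria*: "we request a release of medical records from each participant to confirm their eligibility for the study" and, as a second purpose of the same release, "to ascertain whether potential donors have contacted local transplant centers to be evaluated as donors on behalf of participants". No listing condition is attached.

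Listing is itself part of the primary outcome. The six steps end with "and 6) being listed at a transplant center". How they are collected is also stated: "Pursuit of LRT will be assessed via questionnaires administered via telephone questionnaire at baseline, 1 month, 3 months and 6 months follow-up time periods". Donor inquiry at a center is not one of the six steps.

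**The concern.** Ascertainment of an outcome should not depend on something the treatment can change. Here the described trigger for contacting a center is a self-reported listing, which the trial hopes to make more frequent. If the intervention raises listing, centers are contacted for more people in the intervention arms, and for a different mix of people. Any between-arm contrast in inquiries then mixes an effect on donors with an effect on who was looked up.

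The trigger also fits poorly with the trial's own structure. Identifying a potential donor and being listed are separate steps, so a donor can exist for an unlisted participant. The financial program reimburses the costs of donor evaluation, and neither its description nor the section on enrolling donors requires the recipient to be listed. Read literally, the study could reimburse a donor's evaluation visit without asking the center about that donor.

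The measure deserves care because it is obtained from a third party in all arms, whereas the pursuit steps come from telephone interviews. Use of the financial program applies to one arm only.

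**Working it through.** **No figure to reproduce.** The article gives no listing rate, inquiry rate or power statement for this measure. What can be done is to bound how many participants the literal rule would reach and to illustrate the direction of bias.

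**Inputs**
- Arm size: 70 in each of three arms, 210 in total (*Randomization*).
- Planning rates for at least one new step at 6 months: "30% in Usual Care, 50% in PREPARED group, 60% in PREPARED plus Financial Assistance group" (*Sample size and power*).
- Assumption: reporting wait-list registration is the same event as the listing step.

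**Bound on the number queried.** A new listing counts as a new step, so the expected number newly listed in an arm cannot exceed 70 × the planning rate.

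| Arm | Newly listed, at most | Not newly listed, at least |
|---|---|---|
| Usual Care | 70 × 0.30 = 21 | 49 |
| PREPARED | 70 × 0.50 = 35 | 35 |
| PREPARED plus Financial Assistance | 70 × 0.60 = 42 | 28 |
| Total | 98 (98/210 = 47%) | 112 (112/210 = 53%) |

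If b participants are already listed at baseline, they would be queried too, and the lower bound becomes 112 − b. The article does not give b.

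The 98 is a ceiling, reached only if everyone who takes any new step is listed. With an assumed listing share equal in all arms, the rule reaches:
- 10%: 21 of 210, leaving 90% not queried
- 20%: 42 of 210, leaving 80%
- 30%: 63 of 210, leaving 70%
- 60%: 126 of 210, leaving 40%

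**Direction of bias.** All rates here are assumed. Suppose the intervention has no effect on inquiries, with a true rate of 20% in both of two arms, but listing is 10% in one and 30% in the other.

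1. *Unlisted participants counted as having no inquiry*, inquiry independent of listing. Observed rates are 0.20 × 0.10 = 2% and 0.20 × 0.30 = 6%. The threefold difference comes from look-up alone.
2. *Analysis restricted to listed participants.* Let those who would be listed anyway have a 50% inquiry rate, and the extra participants listed because of the intervention 10%. The rates are 50% and (0.10 × 0.50 + 0.20 × 0.10) / 0.30 = 0.07 / 0.30 = 23%. The intervention now looks harmful.

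The same absence of effect can therefore appear as benefit or harm, depending on how unlisted participants are handled, and the article does not say how that is.

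**Whether a route to everyone exists.** The release is requested from each participant, and donor contact with centers is one of its two purposes. It is also used to confirm eligibility, and *Recruitment of participants* places random assignment after that confirmation. The release therefore appears to precede randomization, so limiting look-ups to signers would not select on anything the intervention changed.

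**The case against.** The strongest reply is that the sections can be read together: consent and ascertainment are general, and the wait-list sentence describes one action triggered by a telephone report. The article is a condensed account, and the full protocol may describe the other route. This has force and rules out several stronger readings that a reader might infer.

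- *That centers are contacted only for listed participants, so other inquiries are never found.* The word only is not in the text, and the general release leaves another route open. What stands is that no procedure is described for unlisted participants.
- *That the article flatly contradicts itself by promising the measure in all study groups.* That sentence follows one limited to the two intervention groups. It most naturally means that Usual Care is included too, not that every participant is queried. The sharper tension is between the unconditional release and the conditional contact.
- *That listing is purely a post-randomization status.* Pursuit steps are also asked about at baseline, and participants may have been on dialysis for up to a year, so some may already be listed. New listing is still post-randomization.
- *That most inquiries in every arm would go unsought.* No listing rate is documented. The planning rates allow up to 60% newly listed in the combined arm, so a majority not queried is not forced there.
- *That the trial's main result is compromised.* The primary outcome is collected by telephone from all participants, and donor inquiry is not part of it.

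It is also fair to say that *Data analysis* specifies no comparison of donor inquiries, so the biased analyses above are possibilities and not stated plans. But assessing the measure in every arm invites such a comparison, and a later analysis plan cannot recover inquiries that were never looked up.

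**Conclusion.** The point holds for an additional measure. The described procedure ties look-up to a self-reported status that is an outcome step and that the intervention may change, while the release was requested from each participant without that condition. Followed literally, the rule gives a between-arm comparison of inquiries that is not a comparison of randomized groups and can err in either direction.

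At least 112 of 210 participants (53%) would not be queried, less those already listed at baseline. This rests on the planning rates being right and on equating reported registration with the listing step. The size of any bias cannot be estimated from the article. The change is worth making because it removes a real source of bias cheaply. It does not bear on the primary analysis.

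**What to change.** Reconcile the eligibility section with the two statements in the outcomes section. Remove the wait-list condition, and state that local transplant centers will be queried about donor inquiries for every randomized participant with a signed release, in all three arms and over the same follow-up period. Compare arms by randomized group, and report by arm how many participants had no release.

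The cost is look-ups for up to 3 × 70 = 210 participants, under releases already requested and without new patient contact. Masking the person doing the look-up to arm is optional.

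If this is not feasible, state that the measure is descriptive among participants who report being listed and will not be presented as a randomized comparison.

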	**PATIENT**			
**Measure**	**Baseline**	**1**	**3**	**6**
		**Month**	**Month**	**Month**
**Current Treatment Information**				
Date and Place of Initiation of Dialysis	X			
Presence of AV^*^ Fistula or AV Graft	X			
Presence of Peritoneal Catheter	X	X	X	X
**Exposure to Information about Kidney Disease Treatment**				
In Center Hemodialysis Information	X	X	X	X
Home Hemodialysis Information	X	X	X	X
Peritoneal Dialysis Information	X	X	X	X
Kidney Transplant Information	X	X	X	X
Live Donor Kidney Transplant Information	X	X	X	X
**Discussions with Health Care Providers about Kidney Disease Treatment**				
Occurrence of Physician Discussions-Nephrologists	X			
Satisfaction with Patient-Physician Discussions	X			
Physician Recommendations Regarding LRT*	X			
**Belief & Knowledge about Treatment for Kidney Failure**, **Interest in LRT**				
Beliefs About Treatment for Kidney Failure	X	X	X	X
Knowledge of LRT	X	X	X	X
Interest in LRT	X	X	X	X
Consideration of LRT (stage placement)	X	X	X	X
**Elements of Shared Decision Making**				
Stage in Decision Making [43]	X	X	X	X
Decision Self-Efficacy [43]	X	X	X	X
Decisional Conflict Scale [44]	X	X	X	X
Interest in Switching Renal Replacement Therapy				
**Pursuit of LRT**, **Barriers to Completing Behavior Stages**				
Quality of Family Discussion	X	X	X	X
Information on Donor	X	X	X	X
Barriers to Patient-Family Discussion	X	X	X	X
Barriers to Patient-Physician Discussion	X	X	X	X
Barriers to Starting Evaluation	X	X	X	X
Barriers to Completing Evaluation	X	X	X	X
**Mediators and Correlates of Pursuit of LRT**				
Trust in Medical Care [53,54]	X			
In-Center Dialysis Care - Nephrologist Communication, Receipt of Information	X	X	X	X
Family Functioning [46]	X			
Depressed Mood PRIME-MD/PHQ^*^[48]	X		X	X
Social Function - Emotional Support, Instrumental Support, Informational Support, Social Isolation [47]	X			
Personal Financial Well-being Scale [49]	X			
Charlson Comorbidity Index [55]	X			
Sociodemographic Information	X			
**Assessment of Book and Video**				
Assessment of Book and Video		X	X	X
**Health Literacy and Numeracy**				
Rapid Estimate of Adult Literacy in Medicine (REALM) [50]	X			
Subjective Numeracy and Risk Numeracy [51,52]	X			

*****Abbreviations are as follows: living related kidney transplantation (LRT); arteriovenous (AV); primary care evaluation of mental disorders/patient health questionnaire (PRIME-MD/PHQ).

### Statistical considerations

#### Data analysis

Randomly assigned intervention group (i.e. Usual Care, PREPARED, PREPARED plus Financial Assistance) will be the main independent variable for intent-to-treat analyses. In our primary analyses, we will assess the proportion of participants in each group achieving at least one new LRT pursuit behavior over 6 months. We will use multivariable models (e.g. logistic regression) to assess differences in the odds of achieving LRT pursuit behaviors among study groups while adjusting for study site characteristics and other baseline characteristics found not to be balanced by randomization. Secondary analyses will include exploratory analyses among persons within subgroups defined post-randomization--for example, analyses among persons with greater versus lesser knowledge of LRT at baseline. We will conduct primary analyses under the assumption that data is missing at random, however, we will also perform sensitivity analyses based on other scenarios (i.e. patterns of missing data) to evaluate the robustness of our assumptions.

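### The adjusted comparison of arms picks baseline covariates by observed imbalance and leaves unclear whether recruitment site, the blocking factor, is a model term

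*Protocol article*

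**What the plan says.** Four statements in the protocol article bear on this.

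- **Endpoint (Data analysis).** The primary analyses begin with a binary outcome: "we will assess the proportion of participants in each group achieving at least one new LRT pursuit behavior over 6 months".
- **Model (Data analysis).** The next sentence gives the comparison of arms: "We will use multivariable models (e.g. logistic regression) to assess differences in the odds of achieving LRT pursuit behaviors among study groups". The same sentence then sets the rule for which covariates enter that model: "adjusting for study site characteristics and other baseline characteristics found not to be balanced by randomization". It names no covariate in advance and gives no criterion for imbalance.
- **Allocation (Randomization).** There are three arms of 70, and "Randomization is blocked by recruitment site to ensure equal allocation within each dialysis facility".
- **Baseline measurement (Measures assessed through interventions).** The six steps that define pursuit of LRT are asked about before follow-up as well as during it: "Pursuit of LRT will be assessed via questionnaires administered via telephone questionnaire at baseline, 1 month, 3 months and 6 months follow-up time periods".

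**The concern.** After a sound randomization, any baseline imbalance is due to chance. What makes a covariate worth adjusting for is how well it predicts the outcome, and an imbalance check does not measure that. Under the stated rule a variable with no bearing on the outcome can enter the model, while a prognostic one stays out if it happens to be balanced. The adjusted estimate then depends on which variables fell out unevenly and, since no criterion is given, on who judges the unevenness.

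The site wording raises a second question. Randomization is restricted by recruitment site, so the analysis should reflect site. Characteristics of a facility are not its identity and need not absorb all the variation between facilities. If site is left out and sites differ, the blocking makes arm comparisons more precise than the model recognizes, and the test becomes conservative.

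At stake are power and the credibility of the adjusted result. The validity of the trial is not in question.

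**Working it through.** **1. The plan's own power figures.** Inputs from Sample size and power: 70 per arm and rates of "30% in Usual Care, 50% in PREPARED group, 60% in PREPARED plus Financial Assistance group". Alpha and sidedness are not stated; two-sided 0.05 is assumed.

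*Trend* (Cochran-Armitage, scores 0, 1, 2). Mean rate 0.4667.
- Signal: 70 × (0.60 − 0.30) = 21.
- Null SD: √(0.4667 × 0.5333 × 70 × 2) = 5.903.
- Alternative SD: √(70 × (0.21 + 0.24)) = 5.612.
- Power: Φ[(21 − 1.96 × 5.903)/5.612] = Φ(1.68) = 95.4%.

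*Pairwise, 30% v 60%.*
- Null SE: √(2 × 0.45 × 0.55/70) = 0.0841.
- Alternative SE: √((0.21 + 0.24)/70) = 0.0802.
- Power: Φ[(0.30 − 1.96 × 0.0841)/0.0802] = 95.4%; 91.8% at 0.025 and 89.1% at 0.0167.

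Both claims of more than 80% are reproduced.

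**2. The contrast where adjustment matters most.** For PREPARED v Usual Care at the assumed 30% v 50%, the same formula gives Φ[(0.20 − 1.96 × 0.0828)/0.0811] = 67.9% at 0.05, and 57.0% at 0.025. The plan does not claim power for this contrast.

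**3. Simulation.** 210 patients; 10 sites of 21, with 7 per arm per site; logistic Wald tests; 4,000 null runs (30% in all arms) and 2,000 runs at 30/50/60%. Site effects are normal on the log-odds scale. One standardized baseline covariate stands in for prior LRT steps, alongside nine noise covariates. Imbalance selection means ANOVA p < 0.05 across arms. The number of sites, the effect sizes and the 5% threshold are all assumptions.

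Power, PREPARED v Usual Care, two-sided 0.05:

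| Site SD | Baseline log-OR per SD | Imbalance-selected | Site only | Site + baseline | Gain (points) |
|---|---|---|---|---|---|
| 0 | 0 | 66.5% | 68.4% | 68.8% | 2.3 |
| 0.5 | 0.5 | 66.9% | 70.4% | 73.5% | 6.6 |
| 0.5 | 1.0 | 68.2% | 70.1% | 78.8% | 10.6 |
| 1.0 | 1.0 | 69.9% | 75.0% | 82.0% | 12.1 |

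At 0.025 the moves are 56% to 60%, 55% to 63%, 57% to 69% and 59% to 74%. Monte Carlo SE of a power figure is about √(0.7 × 0.3/2000) = 1.0 point.

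Null rejection at nominal 5%, same contrast, rows in the same order:
- Imbalance-selected: 5.0%, 4.5%, 4.5%, 3.6%.
- Site + baseline: 5.7%, 6.0%, 5.8%, 5.4%.

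Monte Carlo SE is about √(0.05 × 0.95/4000) = 0.3 points.

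**4. Reading the results.**
- The baseline covariate entered the imbalance-selected model in about 4-6% of trials however prognostic it was. That is simply the level of the imbalance test.
- At site SD 1.0 the wholly unadjusted model also rejected only 3.8% under the null, so the conservatism comes from omitting site, not from selection.
- The site + baseline model used fixed site indicators, which reject slightly too often here. Some of each gain reflects that, and the 2.3 points in the first row should not be read as real precision.
- The imbalance-selected model had no site-characteristic terms. If the planned terms capture much of the between-site variation, the site part of the gain shrinks; it is an upper bound.

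**The case against.** **Naming covariates is work for the analysis plan.** Which covariates enter would indeed be no finding if the article were silent. It is not silent: it states a selection rule, and that rule is what is criticized.

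**Site may already be covered.** The sentence can be read as putting site terms in regardless of balance, with only the other covariates depending on imbalance. This stands in part. A reader might infer that the blocking factor is ignored, but the text is ambiguous and does not exclude it.

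**No error-rate harm.** A reader might infer that data-driven selection inflates type I error. The simulation shows none under one fixed rule; the imbalance-selected test was at or below its nominal level. Discretion without a stated criterion could add inflation, but that was not simulated. Nor would counting the listed baseline measures and computing the chance that one is flagged give an error rate: no test level is stated, the measures are not independent, and a non-prognostic covariate does little harm among 210 patients.

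**The gain is not a smaller standard error.** This is correct for the odds ratio. Unadjusted, the log-odds ratio is ln(0.7/0.3) = 0.847 with SE √(1/21 + 1/49 + 1/35 + 1/35) = 0.354. In simulation with site SD 0.5 and baseline log-OR 1.0, adjustment raised the mean estimate from 0.860 to 1.137; a separate run gave mean SE rising from 0.36 to 0.43. The ratio goes from 0.860/0.36 = 2.39 to 1.137/0.43 = 2.64. Power rises because the conditional odds ratio grows faster than its SE. Power formulas that enlarge the sample by a share of explained variance belong to linear models and are not used here.

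**Baseline steps may not predict much.** The document does not say how they relate to outcome. Because the endpoint counts only new behaviors, someone with more steps behind them has fewer left, so even the direction is uncertain. They are a natural candidate, but nothing supports calling them the strongest predictor.

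**The plan powered other contrasts, and this may not be the primary model.** Both points stand. The plan's power statements concern the trend and a 30-point difference. The primary analyses are introduced with group proportions, and the model follows in the next sentence.

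**Conclusion.** The point holds in limited form. The stated rule makes the adjusted comparison data-dependent and admits a prognostic baseline variable only by luck. The site wording does not settle whether recruitment site is a term.

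The consequences are lost power, a conservative test if site variation is large and site is omitted (3.6% against a nominal 5% at site SD 1.0), and room for discretion. For 30% v 50% at two-sided 0.05, the power at issue ranges from about 2 points if neither variable is prognostic, which is hardly a real gain, to about 7-12 points under moderate to strong assumptions. These figures rest on an assumed 10 sites, assumed effect sizes, an assumed imbalance threshold and a comparator without site terms.

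The change is worth making because it costs almost nothing. The documents do not support a claim that the planned analysis is invalid or its type I error inflated.

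**What to change.** Replace the adjustment clause with wording such as:

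> The adjusted model includes arm, recruitment site and the number of LRT steps already achieved at baseline, regardless of observed balance.

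Then:
- State how site enters. Because sites may be small, use a random intercept, a conditional likelihood or a Mantel-Haenszel type approach; fixed indicators gave null rejection of up to 6.0% in the simulation. The random-intercept and conditional versions were not simulated, so check the chosen method at the actual number and size of sites.
- Report standardized risk differences alongside odds ratios, so that the result is on the percentage scale used in Sample size and power. A conditional likelihood does not give these directly, which is a reason to weigh the alternatives.
- Keep imbalance-driven adjustment as a sensitivity analysis only.
- Say whether the adjusted model or the comparison of proportions is primary.

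The cost is a few lines of analysis wording, dated before outcomes are examined by arm. Site and baseline LRT steps are already recorded, and neither the design nor the sample size changes.
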